## Definition of Serious Adverse Event (SAE)

An SAE is any untoward medical occurrence regardless of cause or relationship to study drug that:

- Results in death.
- Is life-threatening. Any adverse experience that places the subject, in the view of the investigator, at immediate risk of death from the reaction as it occurred (i.e., it does not include a reaction that, had it occurred in a more serious form, might have caused death).
- Requires in-patient hospitalization (excluding the hospitalization required by the study) or prolongation of existing hospitalization.
- Results in persistent or significant disability or incapacity.
- Is a congenital anomaly/birth defect.
- An event that required intervention to prevent permanent impairment or damage.
- Important medical events that do not result in death, are not life-threatening, or do not require hospitalization may be considered serious adverse events when, based upon appropriate medical judgment, they might jeopardize the subject and might require medical or surgical intervention to prevent one of the outcomes listed above.

## Safety Reporting Procedures

All observed or volunteered adverse events regardless of treatment group or suspected causal relationship to study drug will be recorded on the adverse event pages of the case report form. Events involving adverse drug reactions, illnesses with onset during the study, or exacerbations of pre-existing illnesses other than malaria should be recorded. Exacerbation of pre-existing illness, including the disease under study, is defined as a manifestation (sign or symptom) of the illness that indicates a significant increase in the severity of the illness as compared to the severity noted at the start of the trial. It may include worsening or increase in severity of signs or symptoms of the illness, increase in frequency of signs and symptoms of an intermittent illness, or the appearance of a new manifestation/complication. Exacerbation of a pre-existing illness should be considered when a patient/subject requires new or additional concomitant drug or non-drug therapy for the treatment of that illness during the trial. Lack of or insufficient clinical response, benefit, efficacy, therapeutic effect, or pharmacologic action should not be recorded as an adverse event. The investigator must make the distinction between exacerbation of pre-existing illness and lack of therapeutic efficacy. In addition, clinically significant changes in physical examination findings and abnormal objective test findings (e.g., laboratory) should also be recorded as adverse events. The criteria for determining whether an abnormal objective test finding should be reported as an adverse event are as follows:

- test result is associated with accompanying symptoms, and/or
- test result requires additional diagnostic testing or medical/surgical intervention, and/or
- test result leads to a change in study dosing or discontinuation from the study, significant additional concomitant drug treatment or other therapy, and/or
- test result leads to any of the outcomes included in the definition of a serious adverse event, and/or
- test result is considered to be an adverse event by the investigator

Merely repeating an abnormal test, in the absence of any of the above conditions, does not meet conditions for reporting as an adverse event.

Any abnormal test result that is determined to be an error does not require reporting as an adverse event, even if it did meet one of the above conditions except for condition #4.

**9.3.1.** **Serious Adverse Event Detection and Reporting**

All serious adverse events will be recorded on the appropriate serious adverse event case report form, followed through resolution by a study physician, and reviewed by a study physician.

All unanticipated problems involving risk to subjects or others, serious adverse events related to participation in the study and subject deaths related to participation in the study should be promptly reported by phone, fax, or email to the following:

Division of Human Subjects Protection (DHSP)

Walter Reed Army Institute of Research (WRAIR)

[contact] (Tel)

[name] (Fax)

[contact]

U.S. Army Medical Research and Materiel Command

Office of Research Protections, Human Research Protection Office

[contact] (Tel)

[contact] (Fax)

[contact]

A complete written report will follow the initial notification. In addition to the methods above, the complete report will be sent to the Walter Reed Army Institute of Research Division of Human Subjects Protection, [name], [name] 20910 and to the U.S. Army Medical Research and Materiel Command, ATTN: MCMR-ZB-PH, [name], and also to the WHO Ethical Review Committee, Geneva, Switzerland, and to the National Ethics Committee for Health Research, Cambodia.

All serious adverse events regardless of treatment group or suspected relationship to study drug must be reported within 24 hours of the event by telephone to the medical monitor

Dr *[name]*

*Battambang Referral Hospital*

*Emmergency and ICU unit*

*[name]*

*[name]*

*[contact]; [contact]*

who will review and report all serious and unexpected adverse events to higher headquarters within the U.S. Army Medical Research and Materiel Command (USAMRMC).

The medical monitor is required to review all unanticipated problems involving risk to subjects or others, serious adverse events and all subject deaths associated with the protocol and provide an unbiased written report of the event. At a minimum, the medical monitor must comment on the outcomes of the event or problem and in case of a serious adverse event or death, comment on the relationship to participation in the study. The medical monitor must also indicate whether he/she concurs with the details of the report provided by the principal investigator. Reports for events determined by either the investigator or medical monitor to be possibly or definitely related to participation and reports of events resulting in death must be promptly forwarded to the WRAIR IRB, the USAMRMC ORP HRPO and the Ethical Review Committee of WHO.

The study clinician will complete a Serious Adverse Event Form within the following timelines:

- All deaths, whether associated or not associated, will be recorded on the Serious Event Form and sent by fax within 24 hours of site awareness of the death.
- Serious adverse events other than death, regardless of relationship, will be reported via fax by the site within 72 hours of becoming aware of the event.

All SAEs will be followed until satisfactory resolution or until the Principal Investigator or Sub-investigator deems the event to be chronic or the patient to be stable.

ICH GCP 6, Section 4.11 require that an investigator notifies the sponsor, regulatory authority(ies) and the local IRB immediately of any serious adverse event, deaths, or life-threatening problems that occur in the study. The SMC will also be informed.

### 9.3.2. Type and Duration of the Follow-up of Subjects After Adverse Events

Adverse events will be followed by the study team until resolved or considered stable. If by Day 42 the AE has not resolved the patient will be followed after the normal observation period. The investigators will collect pregnancy information on any female subject, who becomes pregnant while participating in this study. The investigators will record pregnancy information on the appropriate form. The subject will also be followed to determine the outcome of the pregnancy. Generally, follow-up will be no longer than 6 to 8 weeks following the estimated delivery date. Any premature termination of the pregnancy will be reported. While pregnancy itself is not considered to be an AE or SAE, any pregnancy complication or elective termination of a pregnancy for medical reasons will be recorded as an AE or SAE. A spontaneous abortion is always considered to be an SAE and will be reported as such.

## Halting Rules

### Individual Halting Rules

Individual study subjects will be withdrawn from their randomized dosing arm and receive no further artesunate doses if any of the following values or criteria (representing possible artesunate toxicity) are met:

 **Hematologic**

**** hemoglobin 7 mg/dL (WHO criteria cut-off for severe anemia in severe malaria**)**

 decrease in hemoglobin from baseline of > 3.6 mg/dL (two standard deviations from the Day 0 hemoglobin from uncomplicated falciparum patients enrolled into the previously completed DRT WRAIR Protocol #1263). This may be an over-cautious cut-off and may need to be modified since the Day 0 CBC value is often artificially elevated due to hemoconcentration secondary to dehydration which is often observed in acute malaria patients, and also a drop in blood count is an expected occurrence in patients recovering from malaria especially those with higher baseline parasitemias.

 absolute neutrophil count < 1 x 109 /L

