**Table 2.8: Comparison blood glucose between treatment arms**

Comparisons between treatment arms: parametric (t-test) / non-parametric (Kruskall-Wallis):

|  | | Quinine and Tetracycline | | |
| --- | --- | --- | --- | --- |
| Day 0 | Day 3 | Day 7 |
| AS | Day 0 | 0.67 / 0.59 |  |  |
| Day 3 |  | 0.61 / 0.37 |  |
| Day 7 |  |  | 0.0001/ 0.0001 |

The results of these laboratory assessments showed that over 7 days of treatment the mean HCT fell by 1, the mean RBC count fell by 0.06 and the mean WBC rose by 530 in AS-treated patients. In QT-treated patients the mean HCT rose by 1, the mean RBC count rose by 0.17 and the mean WBC rose by 1377. None of these changes were significantly different from baseline. There are no differences in any of the laboratory parameters between AS and QT treatment groups on Days 0 or 3. The mean RBC, WBC and HCT in AS-treated patients were significantly lower on Day 7 than those in QT-treated patients on Day 7. QT-treated patients had significantly lower mean plasma glucose levels on Day 7 compared to AS-treated patients.

None of the observed laboratory findings were clinically significant nor led to discontinuation of the study drug. However since all patients had uncomplicated malaria the observed differences between treatment groups seen on Day 7 were probably a drug effect. AS is known to depress the compensatory rise in reticulocytes in response to acute malaria and this may have led to the observed differences in HCT and RBC seen on Day 7. Similarly, quinine is known to have an insulin-like hypoglycemic effect that may account for the observed lower mean plasma glucose values seen on Day 7.

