## Exclusion Criteria

Subjects presenting with any of the following will not be included in the study:

1. Pregnant women, nursing mothers, or women of childbearing potential who do not use an acceptable method of contraception (as described in Inclusion Criteria, #3)
2. Mixed malaria infection on admission by malaria smear
3. A previous history of intolerance or hypersensitivity to the study drug artesunate or to drugs with similar chemical structures, such as artemether, artemisinin or dihydroartemisinin
4. History of malaria drug therapy administered in the past 30 days
5. Previous participation in this trial, or participation in any other studies involving investigational or marketed products, concomitantly or within 30 days prior to entry in the study
6. History of significant cardiovascular, liver or renal functional abnormality or any other clinically significant illness, which in the opinion of the investigator would place them at increased risk.
7. Symptoms of severe vomiting (no food or inability to take food during the previous 8 hours).
8. Signs or symptoms of severe malaria (adapted from WHO recommendations (2003): prostration, impaired consciousness, respiratory distress, convulsions, systolic blood pressure < 70 mm Hg, abnormal bleeding, severe anemia with hemoglobin <8 g/dL or HCT <24%, hyperparasitemia at >4% parasitized red blood cells).
9. Unable and/or unlikely to comprehend and/or follow the protocol

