## Laboratory Evaluations

### Laboratory Evaluations/Assays

- Hematology (hematocrit, RBCs, WBCs, platelets) on days 0, 3, 6, and 14 (or whenever clinically warranted) (2 ml per blood draw).
- Glucose on days 0 (or whenever clinically warranted) (2 drops per blood draw).
- ALT on days 0, 3, 6, and 14 (or whenever clinically warranted) (1 ml per blood draw)
- Urine pregnancy test: Urine beta-HCG test. All female subjects will undergo a pregnancy test at baseline. Pregnant women will not be eligible for entry into the study.
- Urine (approximately 5ml) will also be collected from all participants to be frozen for probable antimalarial drug screening on the day 0 sample at a later date.
- Peripheral blood smears up to 8 times on Day 0 from blood drawn for other reasons or by finger prick blood smear at 12 and 18 hours and then 4 times daily until negative on 2 successive occasions. Thereafter blood smears will be performed on Days 14, 21, 28, 35, and 42 :
  - To determine species of parasite
  - To quantify parasitemia

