** Complete Blood Counts**

 Hemoglobin and white blood cell counts with differential to determine the absolute neutrophil count will be compared at designated time points between dosing arms.

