# PCR sample 8 ml on admission and day of failure; all other samples 3-4 drops blood taken with malaria blood smear

“ CBC and ALT to be collected on Day 14 only

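### Both hemoglobin halting limits are printed in mg/dL instead of g/dL, and the listed hematology panel has no differential for the ANC halting rule and outcome

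*Protocol*

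**What the plan says.** The individual halting rules in section 9.4 withdraw a subject from the assigned arm and stop artesunate when any listed criterion is met. There are three hematologic criteria:

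- an absolute hemoglobin limit of "7 mg/dL (WHO criteria cut-off for severe anemia in severe malaria";
- a "decrease in hemoglobin from baseline of > 3.6 mg/dL (two standard deviations from the Day 0 hemoglobin" of uncomplicated falciparum patients in an earlier study, #1263;
- "absolute neutrophil count < 1 x 109 /L".

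Exclusion criterion 8 in section 5.4 states hemoglobin in a different unit: "severe anemia with hemoglobin <8 g/dL or HCT <24" percent.

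Section 6.2.1 defines the blood tests as "Hematology (hematocrit, RBCs, WBCs, platelets) on days 0, 3, 6, and 14", or when clinically warranted, at 2 ml per draw. It names neither hemoglobin nor a differential. Section 8.1.2 makes both a primary laboratory outcome: "Hemoglobin and white blood cell counts with differential to determine the absolute neutrophil count will be compared at designated time points between dosing arms". The Appendix A row says only hematology, and its footnote reads "CBC and ALT to be collected on Day 14 only" without listing components.

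**The concern.** The two hemoglobin limits fail in opposite directions if applied as printed. The absolute limit could never fire, and the fall limit would be met by almost any decrease. An individual halt ends dosing, and under the cohort rules more than four halts in one arm for the same event halt that arm.

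The second problem concerns what is measured. A site that runs the section 6.2.1 list has no neutrophil count, so it cannot apply the neutropenia halt or supply the between-arm ANC comparison. ANC is a relevant signal here: Table 1 names it among the findings in healthy volunteers given 8 mg/kg/day IV for 3 days and in rhesus at 32 mg/kg/day. The Safety Monitoring Committee's first review covers the safety laboratory results of the first five high-dose subjects, and under that list those results could lack ANC.

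**Working it through.** **Inputs.** Halting limits: section 9.4. Hemoglobin–hematocrit pairing of 8 g/dL with 24%: exclusion criterion 8. ARC1 Day 0 hematocrit SD of 5.3 points (artesunate arm): Table 2.5. ARC1 mean change, artesunate arm: "over 7 days of treatment the mean HCT fell by 1", from the text after Table 2.8. ARC1 artesunate WBC values: Table 2.3.

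**The plan's own figure.** The 3.6 is described as two SDs, so it implies an SD of 3.6 / 2 = 1.8. The hemoglobin SD from study #1263 is not in the protocol, so 3.6 cannot be reproduced directly. A proxy is available:

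- hematocrit-to-hemoglobin ratio = 24 / 8 = 3;
- two SDs of hematocrit = 2 × 5.3 = 10.6 points;
- in hemoglobin, 10.6 / 3 = 3.53 g/dL.

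This is within 2% of 3.6 (3.6 / 3.53 = 1.02) if the unit is g/dL. It comes from another study and another measure, so it is consistent with g/dL rather than proof of it.

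**The limits as printed and as evidently meant.**

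| Limit | In mg/dL, as printed | In g/dL |
|---|---|---|
| Absolute, 7 | 0.007 g/dL; hematocrit 0.007 × 3 = 0.021% | hematocrit 7 × 3 = 21% |
| Fall, 3.6 | 0.0036 g/dL; 0.0036 × 3 = 0.0108 point | 3.6 × 3 = 10.8 points |

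The ARC1 mean fall of 1 hematocrit point is 1/3 g/dL, or 333 mg/dL, and 333 / 3.6 = 92.6 times the printed limit.

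**Illustration of a literal reading.** Assume normally distributed changes in hematocrit with mean fall 1, SD 5.3 at each time, and within-patient correlation ρ between 0.5 and 0.8. None of the ρ values is in the protocol. The SD of the change is √(2 × 5.3² × (1 − ρ)).

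| ρ | SD of change | Share with fall > 0.0108 point | Share with fall > 10.8 points |
|---|---|---|---|
| 0.5 | 5.30 | 57% | 3.2% |
| 0.65 | 4.43 | 59% | 1.4% |
| 0.8 | 3.35 | 62% | 0.2% |

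**ANC from the listed panel.** The limit of 1 × 10⁹/L is 1,000/µl. The neutrophil share at which the rule switches is 1,000 divided by total WBC:

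- lowest ARC1 artesunate Day 7 WBC: 1,000 / 3,000 = 33.3%;
- lowest Day 3 WBC: 1,000 / 3,050 = 32.8%;
- Day 7 median WBC: 1,000 / 6,600 = 15.2%.

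At any total WBC above 1,000/µl the rule is undecided without a differential.

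**Whether CBC in Appendix A settles it.** The ARC1 safety section says that complete blood counts were done by the manual method at this site, yet Tables 2.1 to 2.6 report only RBC, WBC and hematocrit. In this protocol's own usage, the term does not guarantee a hemoglobin or a differential.

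**The case against.** The strongest reply on units is that the slip corrects itself. The 7 is labelled a severe-anemia cut-off, and the 3.6 is described as two SDs and as perhaps over-cautious. Neither description fits 0.007 or 0.0036 g/dL, and clinicians would probably read g/dL. That stands: the literal-reading figures show the size of the printed error, not an expected outcome.

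On the differential, section 8.1.2 already requires it, so section 6.2.1 may be only an abbreviated list that staff would read together with 8.1.2 and 9.4. This shows intent. It does not remove the conflict, because section 6.2.1 is where the tests to run are itemised.

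The effect on dosing is also narrow. Artesunate runs from Day 0 to Day 6, so after baseline only the Day 3 draw, and the Day 6 draw if read before the last dose, can trigger a scheduled hematologic halt. Investigator and committee discretion and the pause after five high-dose subjects operate regardless. This limits the consequence, but discretion does not replace a stated threshold or an unmeasured count. The ANC outcome comparison is affected at every scheduled time point.

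**Conclusion.** Both parts hold. The two hemoglobin halting limits are misprinted by a factor of 1,000 in a rule that ends dosing. Context points clearly to g/dL, so a correction is needed but a rethink of the thresholds is not. The assay list omits hemoglobin and the differential. The first can be approximated from hematocrit at the 3:1 ratio implied by exclusion criterion 8; the second has no substitute. One of three hematologic halting criteria, and the ANC part of a primary laboratory outcome, therefore cannot be evaluated from the panel as listed.

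The unit and panel findings rest on the text alone. The 3.53 g/dL check assumes that the ARC1 hematocrit SD and the 3:1 ratio are fair proxies for study #1263. The neurologic, gastrointestinal and genitourinary criteria, the cohort rule as it applies to them, and the efficacy comparison are unaffected.

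**What to change.** 1. In section 9.4, change mg/dL to g/dL in both hemoglobin limits. The values themselves remain for the clinicians and the Safety Monitoring Committee.
2. In section 6.2.1 and the Appendix A hematology row, list hemoglobin and a WBC differential with ANC, alongside hematocrit, RBCs, WBCs and platelets, on Days 0, 3, 6 and 14.
3. If hemoglobin is to be derived from hematocrit, state the conversion and where it applies.

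The cost is wording in three places, plus case report form fields if they are not already there (the forms are not in the document). Scheduled work is four hemoglobin readings and four differentials per subject on the existing 2 ml sample. With up to 190 enrolled, that is at most 190 × 4 = 760 of each; failure-day and clinically warranted tests would add to it. No additional scheduled blood draw is needed.

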** Neurologic**

- obtundation,
- new or worsening ataxia,
- > 1 seizure

** Gastrointestinal or Genitourinary**

- visibly bloody stools, not due to another etiology
- visible hematuria or hemoglobinuria, not due to another etiology

### Cohort Halting Rules

 more than 30% failures in one of the arms detected by Day 28 in a preliminary efficacy analysis which will be performed after enrollment of 50% of the subjects into this arm.

 >4 individual halts in the same arm for the same adverse event

 >1 SAEs in any enrolment arm

 This study or part of this study may be terminated or suspended at any time at the discretion of the PI or SMC.

If a study or part of a study is terminated or suspended for any reason, the investigators will promptly inform the institutions and the regulatory authorities, which will be informed and provided the reason(s) for the termination or suspension by the investigator/institution/SMC. The patients should be notified, with IRB guidance.

### Enrolment Pause in Arm 3 for Safety Monitoring

New subject enrolment will be temporarily suspended after the first 5 subjects have been enrolled into the higher dose (Arm 3, 6 mg/Kg/day) regimen, pending a safety review by the SMC

# Clinical Monitoring Structure

AFRIMS will monitor this study. Regular monitoring visits will be performed by AFRIMS staff trained in GCP and study monitoring under supervision of [name] RN. Training in protocol and procedures will be provided prior to study initiation. AFRIMS will provide pre-study visits, regular monitoring visits, and a post-study visit. Reports will be generated after each visit and sent to PIs and QA Officer at AFRIMS, Thailand.

Medical Monitor (as required by AR 40-7) will be a licensed physician based at the Battambang Hospital, Battambang, Cambodia. His duties include monitoring the study subjects from a medical perspective, reviewing and reporting all serious and unexpected adverse events, ensuring medical care for any such events should they occur, and reporting serious events to higher headquarters. He will perform on-site visits approximately every 3 months and as needed.

## Site Monitoring Plan

The site will be monitored regularly to ensure the human subject protection, study procedures, laboratory, and data collection processes are of high quality and meet GCP/ICH and regulatory guidelines. Monitoring will consist of a pre-study visit, regular monitoring visits, and a post-study visit. A minimum of 10% of all CRFs will be reviewed by the monitors.

## Protocol Deviations

Protocol deviations will be reported to the local IRB and the WRAIR IRB and Human Research Protection Office (HRPO) as part of the annual report. Any deviations that fit the category of “unanticipated problems involving risks to volunteers or others” should be promptly reported. Any deviation to the protocol that may have an effect on the safety or rights of the subject or the integrity of the study must be reported to the WRAIR IRB and to the USAMRMC ORP HRPO as soon as the deviation is identified.

